#### Sample and Recruitment

For this study phase, 50 Ada users will be recruited from the SCA user strand of phase 2 and, if needed, additionally via social media. Considering a dropout rate of 30%, a sample size of 36 is assumed. Of these participants, 15 will be recruited for single semistructured interviews using maximum variation sampling. Sampling will consider the content of the diary-based self-observation, usage behavior of the app, medical indication, and socioeconomic factors. Sample size calculations of the interview phases are based on the 5D model of *information power* by Malterud et al [49].

All participants will receive web-based training on the self-observation period. The diary will be used to document symptoms and events, as well as other expected influencing factors such as stress or quality of life. Furthermore, it will offer structured questions about the use of SCAs and enable the participants to write down their own reports or short “field notes.” Thus, participants will record and describe their experience, and how they dealt with action recommendations, appearing problems, emotions, etc. These notes will be used as a basis for the following semistructured interviews. The interviews will be conducted via video call, audio-recorded, and transcribed verbatim by a researcher from the IGP and the IEHM. The users will receive financial compensation both for the interviews and the participation in the member check meeting described below.

#### Analysis

The diary-based self-observation and the interview transcripts will be analyzed and integrated into cases. Triangulating the self-observation diary data with interview transcripts provides both prospective (longitudinal) and retrospective (narrative) insights. Quantitative results of the diaries (frequency of use, use of health care, symptoms, etc) will be considered as prospective observational outcomes and will be analyzed quantitatively. The user diaries give the opportunity to record detailed situational experiences—feelings and thoughts that probably cannot be remembered or recreated during an interview without them. However, the interviews will provide in-depth reports on values, concepts, gaps in knowledge, etc, that tend to remain invisible in the diaries. The qualitative analysis via Kruse’s integrative basic procedure [43] will provide an overview of the recurring themes and patterns within each case as well as between cases. At the same time, it will allow a more holistic consideration of the data such as the analysis of semantics, grammatical structures, and metaphors to reveal latent meanings and the way users “make sense” of the app and derive meaning and understanding of the recorded events [50]. The qualitative analysis of the study is supported by MaxQDA [51]. A member check with participants of the interviews is planned, in which results of the cases are presented to study participants to enhance rigor.

The aim of the quantitative analysis is to identify meaningful predictors for the use of SCAs, taking the longitudinal data structure into account. A hierarchical model with 2 levels will be performed. Level two will comprise the daily measurements and will be nested in level one, which comprises the participants. The quantitative analysis of the diaries will be performed using a recent version of Microsoft Excel [52] and R Statistics (R Core Team).

### Study Phase 4: Semistructured Interviews With GPs and Health Care Experts

#### Structure

The fourth study phase investigates the possible effects of SCAs on health care delivery, health care providers (module A), and the health care system (module B). As primary care is most affected by patients’ usage of SCAs, we will interview GPs in module A. We will gain more insights into patients’ usage of SCAs and similar application results in potential psychosocial demands, resources, and perceived work-related stress [53], especially regarding workload, work content, work organization, and social environment [54]. Module B aims to deliver a multi-perspective view on possible effects of SCAs on the health care system. To fulfill this aim, we will conduct interviews with health care experts with different backgrounds to assess the state of science of SCAs in practice from a multi-perspective standpoint. Moreover, we aim to identify which potential experts see for the future use of SCAs and to derive quality criteria for SCAs. This study phase will be conducted and reported according to SRQR statement [31].

#### Sample and Recruitment

In module A, the sample will consist of 10 GPs in Germany. We aim to build a heterogeneous sample regarding the GP (age, gender, and race) and their practices (structure and location of the practice, main patient clientele, and availability of web-based services). Sample size calculations of the interview phases in modules A and B are based on the 5D model of *information power* by Malterud et al [49]. An interview guide [55] will be developed, containing questions about preinformed patients and diagnosis in general, questions about SCAs, and similar apps with the example of the Ada app in particular. It will be developed by the IOSM and the help of feedback from the other project partners. The IOSM will apply various forms of sampling such as snowball sampling in the established networks of the IOSM and web-based research to ensure the stated heterogeneity of the sample. Two researchers of the IOSM will conduct the interviews mostly via video call due to the ongoing pandemic. The interviews are expected to last about 45 minutes and will be audio-recorded.

In module B, 10-15 experts on health care systems will be interviewed. Experts will be recruited consecutively and comprise politicians, information technology developers for medical software, patient advocates, representatives from jurisdiction, medical associations, and health insurances. We assume that 10-15 interviews will provide sufficient information power [49]. Each interview guide will be tailored to the respective expert. Possible topics are the implementation of SCAs, recent issues with SCA requirements, and how SCAs influence different players in health care. The interview guides will be developed by the team of the IGP with input from the other project partners. The experts will be contacted via already existing research networks of the project partners. One researcher of the IGP will conduct the interviews mostly via video call. The interviews are planned to last about 45-90 minutes and will be audio recorded.

The expert interviews will provide an information background on the *status quo* of SCAs in health care as well as ideas for future developments. This background is important for the discussion of user experiences (Study phase 3) and for the patient-physician relationship (integrated study phases 3 and 4). All participants will receive financial compensation both for the interviews and the participation in the member check meeting.

#### Analysis

All interviews will be transcribed. In module A, the interviews will be analyzed with reflexive thematical analysis by Braun and Clark [56]. As already stated, this method is used to understand how interview participants “make sense” of their experiences. This allows insight into tacit changes in self-concepts, implicit values psychosocial demands and resources, and perceived work-related stress. Additionally, it allows to conduct an analysis of themes and content provided by the interview partners. The IOSM team will individually evaluate each interview and compare the interviews to analyze common patterns. To ensure quality control and richness of analysis, each interview will be analyzed by 2 researchers, and preliminary results will be continuously discussed with additional researchers from the joint project. The interviews in module B will be analyzed with reflexive thematical analysis by Braun and Clark [56], as we aim to collect and structure the overarching themes and their various dimensions. The same measures for quality control, as described in module A, will be applied. For additional quality control, a member check with interview participants of phase 4 is planned: preliminary results will be presented, and participants will be invited to give critical feedback, which will be integrated into the further analysis.

## Results

The project started in March 2020.

### Study Phase 1: Literature Review

The literature review on ethical, legal, social, and systemic impacts of SCAs was completed in December 2021 and will be published in 2022.

### Study Phase 2: Cross-sectional Survey of SCA Users and SCA Nonusers

The data collection for study phase 2 was finished in July 2021 (n=1074); the publication of the results is planned for 2022.

### Study Phase 3: Diary-Based Self-observation Combined With Semistructured User Interviews

For study phase 3, data collection of the user diaries (n=48) was completed in October 2021, user interviews were conducted in February and March 2022, and publication of the results is planned for 2022.

### Study Phase 4: Semistructured Interviews With GPs and Health Care Experts

The recruitment of experts and GPs (study phase 4) is still ongoing and will be finished in 2022.

## Discussion

### Principal Findings

This protocol describes an interdisciplinary, mixed methods, multiphase research program to comprise the impact of SCAs on the 3 levels (microlevel, mesolevel, and macrolevel) of the health care system [26]. The main findings of the recent exploratory study will be an overview of the ethical, legal, social, and systemic impacts literature on SCAs, epidemiology data of SCAs (as degree of use in Germany, predictors for SCA usage considering user characteristics), requirements of SCA use from a user perspective, a description of SCA user behavior, and a comprehensive assessment of the perspective of GPs and health care experts on SCAs.

Digital health care innovations and their impact on the health care system is a prevailing topic in times of digitalization and the increasing demand of health care professionals such as GPs. In contrast to apps for specialists, user-accessible apps such as SCAs are an unknown variable in the development of health care delivery in the future. Conflicting claims of medical, ethical, and social advantages or disadvantages of SCAs characterize the current state of the debate. Apparently paradoxical effects, as undermining trust in the patient-physician relationship on the one hand, improved exchange on the other hand, may be coexisting or representing different perspectives in scenarios that require further description. The conflicting information about ethical, legal, social, and systemic impacts requires more empiric data to inform and deepen the debate [57].

Little is known about the psychosocial demands and resources of GPs in this context. SCAs are attributed to result in an overuse as well as in an underuse of health care resources. Finally, existing health inequalities may be improved or worsened by their impact. Based on an ScR of the ethical, social, and legal literature, the project will provide evidence, which of these contradicting assumptions is confirmed by the empirical study of the user experiences in the case study at hand. Using SCA as an example of consumer-oriented digital innovations, this study aims to research and integrate questions that are important for the general debate on digital transformation: what is known about the topic? How widespread is the phenomenon? How do users apply the innovation? How does that modulate their behavior and impact their health care usage? How do negotiations with health care providers play out? Which regulatory legislation is necessary? What are the implications for the physicians in particular and the health care system as a whole? However, only collecting data from 1 stakeholder’s perspective without considering possible interactions will generate blind spots. Thus, the main challenge is to consider different stakeholders’ perspectives, wants and needs, and to engage in a transparent debate on the current dynamic developments.

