### Objectives

Owing to the lack of systematic research of SCAs in primary health care, the recent study uses an explorative hypothesis-generating approach in which the abovementioned discussion is informed by 4 foci of interest and the study aims, as stated in the following section.

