#### Focus 3: Patterns and Impact of SCA Use and the User Level

As a goal for the users’ perspective, a comprehensive description of SCA use will be derived. This will comprise the assessment of requirements that are fulfilled or unfulfilled by SCA use. Additionally, we aim to identify the possible risks associated with SCA use and assess how users handle SCA information and action recommendations. SCA effects on user agency, health and eHealth literacy, well-being, and self-care will also be observed.

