### Strengths and Limitations

The projects’ concept integrates different data sources and methods from the very start. The multidisciplinary, multiphase design, and the methods and skills mix of the study partners create a scenario in which methodological strengths are complimentary and perspectives can be negotiated. For example, by limiting recruitment to a single SCA (the Ada app) in the qualitative study phases, we are able to focus the analysis [49]. At the same time, through the representative survey, these qualitative results can be put in a broader context, which will contribute to implications for the health care system. Another strength is the immanent consideration of the user perspective by combining a survey, user diary, and user interviews. In integrating relevant perspectives and plotting study phases to converge in integrated workshops, we present an approach for integrated research in ethics, social, and health sciences. This is possible owing to the long-standing cooperation between all involved partners and previous positive experiences in common projects.

This research project also has limitations: we will not investigate how SCAs perform in terms of medical accuracy. Further, we will not be able to observe direct interaction of patients and physicians in the context of SCAs and see how SCAs influence the patient-physician relationship directly. Moreover, we assessed user and nonuser characteristics through subjective user rating rather than objective measurements (eg, overall health rating of participant). Lastly, we will not directly investigate the effect of SCAs on health care utilization. We will, however, assess parameters considering utilization reported by participants.

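### The Discussion promises evidence on which opposing claim about symptom checker apps is confirmed (over- or underuse of care, inequality better or worse), but the design can only describe and generate hypotheses

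*Protocol article*

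**What the plan says.** **The promise.** In the Discussion, Principal Findings, the protocol article states two pairs of opposing assumptions. On utilization: "SCAs are attributed to result in an overuse as well as in an underuse of health care resources". On equity: "existing health inequalities may be improved or worsened by their impact". It then says that "the project will provide evidence, which of these contradicting assumptions is confirmed by the empirical study of the user experiences"; the sentence closes by limiting itself to the present case study. The same paragraph lists, among the questions to be researched, how use of the app affects use of health care.

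**The stated limits.** Strengths and Limitations says "Lastly, we will not directly investigate the effect of SCAs on health care utilization" and adds that utilization parameters reported by participants will be assessed. The Objectives describe an "explorative hypothesis-generating approach".

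**The design behind the promise.** In study phase 3, "50 Ada users will be recruited from the SCA user strand of phase 2", with social media as a reserve channel. The Study Course section defines a user as someone with at least one past use. The diary runs for 6 weeks, and 15 of the diary participants are then interviewed. The Analysis section of phase 3 lists use of health care among the observational outcomes, but gives the aim of its two-level model as finding what predicts app use.

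**Related wording.** Focus 3 says "SCA effects on user agency, health and eHealth literacy, well-being, and self-care will also be observed".

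**The concern.** Overuse and underuse are statements about a contrast: care sought with the app against care that would have been sought without it. Whether inequality improves or worsens is likewise a statement about change in a gap between groups. The phase named as the source of evidence observes only people already exposed, so it supplies one side of the first contrast and no measure of change for the second.

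The primary outcomes of the project are recommendations to stakeholders. If the promise stands, descriptive accounts from Ada users could be carried into those recommendations as a finding for one side of a contested question. The article's own limitation paragraph would warn against this for utilization only. It says nothing about inequality.

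**Working it through.** The question is whether the design identifies the quantity promised. It is answered by setting the sections side by side. Arithmetic plays only a small part.

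**1. The plan's own figure.** Phase 3, Sample and Recruitment: 50 recruited, 30% dropout, 36 assumed. Check: 50 × (1 − 0.30) = 35, which agrees with 36 to within one participant. The Results section reports 48 diaries collected. Neither number bears on the point, as step 5 shows.

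**2. Utilization.** Write the effect in question as

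Δ = (care used with the app) − (care the same people would have used without it).

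Overuse means Δ > 0 and underuse means Δ < 0.

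- First term: the 6-week diary records use of health care in Ada users, so this is observed.
- Second term: it would need nonusers followed in the same way, or the same people before first use. Phase 3 describes neither, and by the definition of a user the diary starts after first exposure.

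The sign of Δ is therefore not identified.

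**3. Days with and without app use.** The diary records both, so a within-person comparison is possible. It does not supply the missing term, because a new symptom can prompt both opening the app and visiting a physician. The stated two-level model has app use as its outcome, so no described analysis estimates an effect of use on care.

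**4. Inequality.** Improvement or worsening is

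change = (gap between social groups with the apps) − (gap without them).

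- Phase 3 contains users only.
- Phase 2 contains users and nonusers (n=1074 collected). Its case-control analysis uses matched nonusers and a logistic regression with app use as the outcome. It can show who uses the apps and which groups are under-represented among users. It is measured at one time, so it gives no change in a gap.

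**5. Would more diaries help?** Larger n sharpens only the description of users. The 95% half-width for a proportion of 50% is 1.96 × √(0.25/n):

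| n | Half-width |
|---|---|
| 36 | 16.3 points |
| 48 | 14.1 points |

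The missing term stays missing in both rows.

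**6. Consistency of the text.**

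| Section | What it commits to |
|---|---|
| Principal Findings | Evidence on which assumption is confirmed |
| Strengths and Limitations | Effect on utilization not directly investigated; inequality not mentioned |
| Objectives | Exploratory, hypothesis-generating |

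The first row is incompatible with the other two for utilization. For inequality it goes beyond what either phase can show.

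**The case against.** The strongest defence has four parts.

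- **The sentence is qualified.** It limits itself to the present case study, so it may ask only which assumption these Ada users' experiences bear out. Principal Findings also says that seemingly paradoxical effects may coexist and need further description. This narrows the population the claim covers. It does not provide a comparator, and a claim of confirmation needs one even within a case study.
- **It is one Discussion sentence.** The list of expected main findings has a description of user behaviour and no effect on utilization or inequality. This stands, and it limits the weight of the point.
- **The limit is already disclosed.** For utilization that is true. But the limitation does not withdraw the promise and does not reach inequality.
- **Nonusers are studied.** Focus 2 and the phase 2 survey address groups that might be disadvantaged. A reader might infer that the project has no evidence from nonusers at all. That would be wrong: the gap is in the diary phase and in the absence of any measure of change.

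Two other stronger readings are not supported. A reader might infer that the investigators plan to regress care contacts on app use and report the coefficient as an effect. The phase 3 Analysis section specifies no such model. A reader might also take the Focus 3 wording on effects as a firm causal promise. It stands within a goal of describing use from the users' perspective and says only that effects will be observed, so clarification is enough.

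**Conclusion.** The point holds as a mismatch between one stated claim and the design, and between that claim and two other sections of the article. The project can describe user-reported experiences that fit either assumption, and can describe differences between users and nonusers in the survey. It cannot show which assumption is confirmed, for utilization or for inequality.

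The size is qualitative: the direction of the effect is not identified at any sample size. A reader might infer that the flaw is too few care contacts in the diaries. The article gives no contact rate, and a count would not matter, because the missing element is the comparison and not precision.

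The conclusion rests on the article as published, which describes no nonuser diary and no pre-use measurement. Whether the survey asked nonusers about their use of care cannot be judged from it. Even if it did, cross-sectional answers would give an association and not a change.

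This should be corrected, but it does not call the descriptive aims of the project into question.

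**What to change.** 1. **Principal Findings.** Replace the confirmation claim with a statement that the project will describe user-reported experiences consistent with either assumption, describe differences between users and nonusers in the survey, and generate hypotheses. Add that it does not test whether symptom checker apps raise or lower utilization or inequality.
2. **Strengths and Limitations.** Extend the existing limitation from utilization to inequality, and repeat it in the workshop outputs and stakeholder recommendations.
3. **Focus 3.** State that effects on agency, literacy, well-being and self-care mean changes reported by users, or within-person associations with app use.
4. **Diary analysis, only if care contacts are compared by app use.** Stratify by symptom days, using the symptoms the diary already records. This reduces confounding by symptoms but does not turn the comparison into a test of over- or underuse.

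Cost: edits to the text and, if step 4 applies, one stratified summary. No new data are needed. Diary collection ended in October 2021, but the article describes publication as still planned, so the changes can be made in the reporting. The downside is a weaker headline claim.

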### Strengths and Limitations

The projects’ concept integrates different data sources and methods from the very start. The multidisciplinary, multiphase design, and the methods and skills mix of the study partners create a scenario in which methodological strengths are complimentary and perspectives can be negotiated. For example, by limiting recruitment to a single SCA (the Ada app) in the qualitative study phases, we are able to focus the analysis [49]. At the same time, through the representative survey, these qualitative results can be put in a broader context, which will contribute to implications for the health care system. Another strength is the immanent consideration of the user perspective by combining a survey, user diary, and user interviews. In integrating relevant perspectives and plotting study phases to converge in integrated workshops, we present an approach for integrated research in ethics, social, and health sciences. This is possible owing to the long-standing cooperation between all involved partners and previous positive experiences in common projects.

This research project also has limitations: we will not investigate how SCAs perform in terms of medical accuracy. Further, we will not be able to observe direct interaction of patients and physicians in the context of SCAs and see how SCAs influence the patient-physician relationship directly. Moreover, we assessed user and nonuser characteristics through subjective user rating rather than objective measurements (eg, overall health rating of participant). Lastly, we will not directly investigate the effect of SCAs on health care utilization. We will, however, assess parameters considering utilization reported by participants.

